## Abstract

**Background:**

The management of subacromial shoulder pain represents a significant challenge and is typically managed through either physiotherapy, joint injection or surgical intervention. Recent surgical trials have questioned the efficacy and there is a need to improve the evidence base for the non-surgical management of this condition.

The study aims to provide evidence of the feasibility of conducting a randomised controlled trial to compare the efficacy of autologous protein solution (APS) against the current standard of care, corticosteroid injection (CSI) for subacromial shoulder pain. Autologous protein solution (APS) is a blood-derived biological injection which has been shown to have anti-inflammatory effects.

**Methods:**

A parallel-group two-arm randomised control trial will be conducted, comparing APS and CSI for shoulder pain. Fifty patients will be recruited. Feasibility will be assessed by examination of the conversion rate of eligible participants to the total number of participants recruited, whether it is possible to collect the appropriate outcome measures and the levels of retention/data compliance at follow-up dates.

**Discussion:**

CSI is the mainstay of conservative management of subacromial shoulder pain. Trials and systematic reviews have reported differing conclusions, but the consensus view is that any benefits seen from CSI use are most likely to be short-term and there remains a significant number of patients who go on to have surgical intervention despite CSI.

Biological injections, such as APS are being increasingly used, in the anticipation they may offer improved longer lasting outcomes for shoulder pain. However, the evidence to demonstrate the comparative efficacy of CSI versus APS does not currently exist. If feasible, a fully powered study will offer clarity to the treatment pathway of thousands of patients each year with subacromial pain.

**Trial registration:**

The study is funded by the National Institute for Health Research–Research for Patient Benefit, NIHR 201473, Trial Registration Number (ISRCTN12536844: SPiRIT. Shoulder pain: randomised trial of injectable treatments–date of Registration 15/9/2021). Protocol Version V1.0_30Jul2021. IRAS Project ID: 294,982.

## Background

Shoulder pain accounts for 1–2% of all adult consultations with a GP [1]. Of this shoulder pain, around 70% is subsequently attributed to pain arising from the tendons which move and stabilise the shoulder; the rotator cuff. Most commonly these problems are due to inflammation and degeneration of the tendons [2]. Shoulder pain does not always have a favourable outcome with current treatments. Only 59% of patients treated in primary care showing a complete recovery within 6 months [3]. Symptoms may be disabling in terms of the patient’s ability to carry out daily activities at home and the workplace, resulting in time off work. This poses a substantial burden to the individual and society [4–6]. In the USA, the annual financial burden of shoulder pain management has been estimated to be $3 billion [7].

A mechanical explanation for shoulder pain has previously been favoured, whereby contact occurs between the rotator cuff tendons and the overlying bone. This ‘rubbing’ process was felt to result in inflammation of the rotator cuff tendons and nearby structures including a fluid-filled sac called the subacromial bursa. Treatments have historically been directed at reducing this inflammation and rubbing process, either by injections of corticosteroids (to address the inflammation) or surgical intervention to remove some of the bone, which was felt to be rubbing on the tendon. Evidence for the efficacy of both surgical and non-surgical treatments of shoulder pain is limited. A recent publication by the British Elbow and Shoulder Society (BESS) and the British Orthopaedic Association (BOA) highlighted the lack of evidence for a number of interventions used to treat subacromial shoulder pain and the need for research in this area [7]. Given the large number of patients who present to general practice with subacromial shoulder pain, any developments in the treatment of this chronically painful condition will improve the care of thousands of patients each year in the UK.

Currently, Corticosteroid injections (CSI) remain the mainstay of initial treatment in the majority of cases of shoulder pain presenting to both general practice and secondary care. The efficacy of CSI has been tested in a number of trials and subsequently through systematic review. These have reported differing conclusions, but the consensus view is that any benefits seen are most likely to be short-term and there remains a significant number of patients who go on to have surgical intervention despite CSI. In addition to the lack of strong evidence towards the efficacy of CSI, there have also been theoretical and lab-based deleterious effects of corticosteroids on tendon biology reported. CSI might impair the potential for intrinsic tendon repair mechanisms but it may increase the risk of subsequent tendon tearing.

A contemporary understanding of the biology of shoulder tendons, however, gives potential targets for new pharmaceutical or biological treatments. An example of such a strategy is the use of injectable platelet-rich plasma (PRP) or Autologous Protein Solution (APS). PRP is a concentrate of platelet-rich plasma protein derived from whole blood, centrifuged to remove red blood cells. Basic science studies have consistently shown the beneficial effects of PRP on tendons including increased tendon cell proliferation, increased expression of anabolic genes and proteins, and reduced tendon inflammation [8–10]. Unfortunately, these in-vivo findings have not translated to reliable clinical application when subject to clinical trial [11]. APS is prepared using a single-use device that produces a cell concentrate from autologous blood. Conceptually, APS and PRP are very similar as they both aim to isolate anti-inflammatory cytokines and anabolic growth factors from a patient’s own blood, allowing this to be reintroduced at the site of pain. Unlike PRP systems, the APS production process preferentially concentrates anti-inflammatory cytokines production by white blood cells, including IL-1 receptor antagonist and TNF receptor inhibitor [12]. The use of APS is expanding both in the UK and worldwide. Feasibility studies investigating APS in humans, in the context of knee arthritis have been conducted. The treatment also demonstrated a favourable safety profile and was well tolerated [13]. In a further study of patients with arthritis, 46 patients were randomised to receive a single ultrasound-guided injection of APS into the knee, or a single saline injection. Patient-reported outcomes showed improvement in function and reduction in pain. The average change from baseline to 12 months in WOMAC pain score was 65% in the treatment group and 41% in the control group (*p* = 0.02) [14].

### Aims and objectives

There is a recognition that robust evidence must be produced before blood-derived therapies are further introduced into orthopaedic clinical practice [15]. These therapies are freely available in private practice and their use both in the UK and worldwide is increasing. No similar work currently exists to assess the efficacy of APS in treating shoulder pain. Further, to date, no randomised controlled trial (RCT) has investigated a comparison of CSI and APS for shoulder pain. The best means for evaluation of the clinical and cost-effectiveness of APS versus the current standard of care, CSI, would be to undertake a fully-powered multicentre RCT. However, there are uncertainties, specifically regarding recruitment rates and participant retention, that need to be assessed before undertaking a large-scale RCT.

This feasibility study trial aims to:Examine the conversion rate of eligible to randomised participants and total number of participants recruited.Investigate the levels of retention and data compliance at follow-up dates.Assess whether it is possible to collect the appropriate outcome measures (PROMIS Physical Function (upper extremity), PROMIS pain interference questionnaire[16], Oxford Shoulder Score (OSS) [17], Pain visual analogue score (VAS), EQ-5D-5L score [18], Work Productivity Impairment Questionnaire (WPAI) [19] and patient/hospital reported resource use including referral rates for shoulder surgery) at baseline, 3 months and 6 months.Gather data on any complications of either intervention at 6 months.

## Methods

### Trial design and setting

This is a feasibility study of a participant-blinded, parallel group randomised controlled trial. Participants will be followed up clinically as per NHS standard of care. They will also be followed up via questionnaires by the central trial team for a period of 6 months post-treatment. We will recruit 50 participants from two NHS Musculoskeletal (MSK)–triage centres, one in Oxford and the other in Leeds from an existing standard treatment pathway (Fig. 1). The trial will be conducted in accordance with the UK Policy Framework for Health and Social Care Research, the applicable UK Statutory Instruments, (which include the Data Protection Act 2018) and the principles of Good Clinical Practice. The study is following protocol version 1.0 (30 July 2021), Oxford University, Oxford, England, is the sponsor for this trial. The study is funded by the National Institute for Health Research–Research for Patient Benefit, NIHR 201473, Trial Registration Number (please complete).

**Fig. 1 Fig1:**
[figure not shown]
Study flowchart

### Recruitment of participants

As part of usual care for the management of shoulder pain, MSK-triage clinicians will initially prescribe structured physiotherapy to all patients. In addition to structured physiotherapy, patients will be offered an injection into the subacromial space at a separate appointment, as per current clinical practice. GP referrals to the MSK centres were triaged and then eligibility screening then performed following the initial assessment (Fig. 1).

The trial eligibility screening will be undertaken, Fig. 1, and during patient contact to arrange a time for their appointment, they will be asked about their willingness to take part in the study. The SPIRIT team will then contact the patient separately if they are willing to participate and these individuals will be sent a trial invitation letter and participant information sheet (PIS).

### Consent process

The informed consent process will commence when the usual-care clinician confirms the patient should be treated with a therapeutic injection, the participant meets the eligibility criteria for the SPIRIT trial and is willing to take part. They will be informed that they can freely withdraw from the trial or any part at any time without giving a reason.

### Participant eligibility

#### Inclusion

Participant is willing and able to give informed consent for participation in the study.Male or Female, aged 18 years or above.Clinician believes the patient may benefit from injection treatment.

### Exclusion

Participants with a history of significant shoulder trauma (fracture or dislocation in last 5 years).Previous shoulder surgery on the affected shoulder.Contraindications to APS therapy or CSI.A pre-existing neuro-degenerative and/or vascular condition that affects the function of the shoulder.Received CSI/APS injection in 2 months prior to randomisation.The participant is unable to follow trial procedures.Patient does not have access to email/smartphone directly or indirectly.

### Ineligible participants

Screening logs will be kept at each site to determine the number of patients assessed for eligibility and reasons for exclusion. In addition, the number of eligible and recruited patients, and the number of patients who decline consent or withdraw will be recorded. Verbal consent will be requested to store anonymous research data, for example, reasons why they were not eligible, to help inform any future trial.

### Randomisation and blinding

Once informed consent has been obtained, eligibility confirmed and baseline data collected, participants will be randomised at the level of the individual on a 1:1 basis to either a Corticosteroid injection or an Autologous Protein Solution injection. Randomisation will be performed via a secure web-based service provided by the Oxford Clinical Trials Unit. Randomisation will be stratified by centre, duration of symptoms (≤ / > 6 months) and baseline PROMIS pain interference scores.

To avoid bias in the delivery of the intervention and completion of participants’ reported outcomes, the participants are to be kept blind about the treatment that is allocated. This blinding will be achieved by collecting the blood sample required for APS (55 ml), from both groups of patients. In the intervention group, this blood will be used for the preparation of the APS; in the control group, this blood will be sham prepared as APS, but discarded. The injections will then be performed using opaque syringes to prevent unblinding the patient.

Both the APS and the comparator group will undergo structural physiotherapy, the timing of which will begin either before or after the injection has taken place, as per local protocols. Both injections, where possible, will be undertaken under ultrasound guidance.

#### The APS intervention

After the consent and randomisation processes, a 55-ml sample of blood will be obtained and taken to the sample preparation area. The blood will be used for the preparation of the APS injection. The solution will be created as per the manufacturer’s guidelines. It is a two-step process taking 15–20 min—firstly, the blood is separated by centrifuging it, after which it is concentrated in specialised tubes. The total volume of the resultant APS is approximately 3 mls, and does not contain any local anaesthetic. This solution will be delivered in an identical manner to the control treatment but provided in a ‘blinding syringe’ (non-transparent sides).

The APS injection kit is manufactured on behalf of Zimmer Biomet, a medical device manufacturer, it has the trade name of nSTRIDE. nSTRIDE is fully licenced for use in the UK, and the processing machines have the appropriate CE markings.

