### Comparator group

We are not proposing any change of standard care for the CSI group, save that to maintain participant blindness to the intervention the participants will have 55 ml sample blood taken, which will be taken to the sample preparation area. This blood will be discarded in the sample preparation area whilst a sham-centrifuge process is performed in order to maintain participant blinding. The control participants will then receive the CS injection, which contains Depo-medrone (40 mg) mixed with 3 mls of 0.5% bupivacaine local anaesthetic, administered using standard aseptic techniques, but provided in a ‘blinding syringe’ (non-transparent sides).

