### Data collection

At baseline demographic data, patient function and pain data using the PROMIS physical function, PROMIS Pain interference, Oxford Shoulder Score, VAS and Work Productivity Impairment questionnaires will be collected after the participant has provided consent. Participants will also be asked to complete the EQ-5D-5L health-related quality-of-life questionnaire to indicate their typical health status. All case report forms (CRFs) including screening, consent, randomisation and baseline assessment will be completed online on the REDCap database.

Data collection will be divided into two phases, early and late phase follow-up:*Early*—participants will receive a weekly text/email/phone call (according to participant preference) up to week 8 post-randomisation with a link to a visual analogue scale (VAS) asking them to indicate their level of pain in the previous 24 h and whether during that week if they have taken any painkillers for their injury.*Late*—at 3 and 6 months post-randomisation, participants will be contacted by the Oxford central study office via automated SMS or email from the REDCap database and invited to complete the PROMIS, OSS, EQ-5D-5L, VAS, WPAI, health resource use and complications questionnaires.

Complication data will be collected from patients at 3 and 6 months post-randomisation. Complications will be patient-reported via their 3- and 6-month questionnaires and verified by research nurses at the site. At 6 months post-randomisation the site staff will be asked to complete a medical notes review to ensure all expected complications are recorded.

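### Randomisation comes before a blood draw that both arms undergo but only APS needs, so a failed draw means non-receipt in the APS arm alone; drawing first is a cheap improvement

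*Protocol article*

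**What the plan says.** The order is stated. The section Randomisation and blinding sets the preconditions for allocation: "Once informed consent has been obtained, eligibility confirmed and baseline data collected, participants will be randomised at the level of the individual on a 1:1". A successful draw is not among them. Under The APS intervention: "After the consent and randomisation processes, a 55-ml sample of blood will be obtained".

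Both arms are bled. Participant blinding is achieved by "collecting the blood sample required for APS (55 ml), from both groups of patients", and the Comparator group section confirms that "the participants will have 55 ml sample blood taken". The timing of the CSI draw is not repeated there. It follows from the randomisation section and from the draw being described within the allocated arm.

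The blood has a different role in each arm. For APS, "The blood will be used for the preparation of the APS injection". For CSI it is thrown away during a sham spin, and the injection does not depend on it.

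The primary outcome is conversion from eligible to randomised. Progression success is 50 patients recruited. Analysis is by allocated group for anyone with at least one follow-up observation (Statistical considerations and data analysis).

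The follow-up origin is given in two ways. Trial design and setting has questionnaires running "for a period of 6 months post-treatment". Data collection counts the weekly pain scores from randomisation, and likewise the later questionnaires: "at 3 and 6 months post-randomisation, participants will be contacted by the Oxford central study office".

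**The concern.** A step that everyone undergoes, and that can fail, sits after allocation when it could sit before it. Before allocation, a failed draw is an exclusion that cannot depend on arm. After allocation, it becomes one-sided non-receipt: the APS participant has no material for the allocated injection, while the CSI participant can still be given theirs.

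Two consequences follow:

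- The as-randomised difference includes some APS participants who did not receive APS, which pulls it towards zero if they fare like controls.
- The two feasibility yardsticks, conversion and the 50 recruited, both stop counting at randomisation or recruitment. A participant who turns out not to be treatable with APS is scored as a success.

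The effect in this study is small. The order matters more if it is carried unchanged into the definitive trial.

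The two follow-up origins are a separate and simpler matter: the same assessments cannot be timed from both events unless those events fall on the same day.

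**Working it through.** **Inputs from the article.** Total 50, allocation 1:1, 40 evaluable needed (20 per arm), 20% loss allowed, standardised difference for the definitive trial 0.1 to 0.3 with 80% power.

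**Assumptions, not in the article.** Draw-failure rate f of 2%, 5% or 10%. Every failed draw in the APS arm leads to non-receipt. Two-sided alpha of 0.05 for the definitive trial.

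**The plan's own figure.** 40 / (1 − 0.20) = 50. It reproduces and is not in dispute. With 1:1 allocation, about 50 / 2 = 25 go to APS.

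**APS participants affected.** Expected number = 25f; chance of at least one = 1 − (1 − f)^25.

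| f | Expected of 25 | Chance of at least one |
|---|---|---|
| 2% | 0.5 | 1 − 0.98^25 = 40% |
| 5% | 1.25 | 1 − 0.95^25 = 72% |
| 10% | 2.5 | 1 − 0.90^25 = 93% |

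Each affected participant is 1/25 = 4 percentage points of the arm. In the CSI arm, the number losing treatment through a failed draw is 0.

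**Dilution.** Write A for the mean under APS, C for the mean under CSI and U for the mean of untreated APS participants. The as-randomised difference is (1 − f)(A − C) + f(U − C). If untreated participants fare like controls (U = C), it shrinks to (1 − f) of its value: 0.98, 0.95 or 0.90. If U differs from C, the second term adds to or offsets this.

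**If the order is carried into the definitive trial.** The required size scales by 1/(1 − f)². Taking d = 0.3, the top of the article's range:

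| f | Size multiplier | Per arm at d = 0.3 (175 undiluted) | Power if left at 175 |
|---|---|---|---|
| 2% | 1.04 | 182 | about 78% |
| 5% | 1.11 | 194 | 76% |
| 10% | 1.23 | 216 | 71% |

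**With randomisation after a successful draw.** Failed draws cause 0 post-randomisation losses in either arm. Conversion falls by the factor (1 − f). The expected number to consent and bleed so as to randomise 50 is 50/(1 − f): 50/0.98 = 51.0, 50/0.95 = 52.6 or 50/0.90 = 55.6.

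**The case against.** The strongest case against has several parts.

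- **Convention.** Randomising after consent, eligibility and baseline, then treating, is a usual order and not an error. That stands, which is why this is offered as an improvement.
- **Estimand.** Inability to prepare APS is part of how deliverable APS is. An as-randomised comparison captures that, whereas drawing first restricts the trial to people already bled successfully. Either choice is defensible. The present order also keeps conversion as a purer measure of uptake. This is a real cost of the change, and separate logging of failed draws largely meets it.
- **Size.** The failure rate is wholly assumed. The article does not say what happens after a failed or short draw, and the full protocol may. This stands.
- **Purpose.** The between-arm comparison is mainly descriptive and admittedly underpowered. This stands for the present study.

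A reader might also infer three stronger things that the documents do not support:

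- **Distorted retention by arm.** Follow-up is remote and analysis is by allocated group, so a failed draw need not remove anyone from follow-up.
- **Staff who know the allocation try less hard at the draw.** Blinding is declared for participants only, but nothing in the article suggests that effort at the draw differs by arm.
- **An established gap between randomisation and injection.** The statement that "patients will be offered an injection into the subacromial space at a separate appointment" describes usual care, with the injection separate from the initial assessment. The APS section runs consent, randomisation, draw and processing in sequence, which is compatible with one visit, and the flowchart is not shown.

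**Conclusion.** The point holds in a limited form. The order of events, the draw in both arms and the one-sided dependence on the blood are all in the text. A failed draw after allocation therefore causes non-receipt in the APS arm only, mildly dilutes the as-randomised difference, and leaves an untreatable participant counted as a recruitment success.

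The expected size here is 0.5 to 2.5 of about 25 APS participants. This rests on an assumed failure rate of 2% to 10% and on failed draws not being recovered. The dilution factors of 0.98 to 0.90 further assume that untreated APS participants fare like controls. None of this threatens the feasibility aims or the stated sample size.

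The mismatch in follow-up origin is a plain textual inconsistency and stands whatever the failure rate. It does not show that assessments would in fact be mistimed.

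**What to change.** 1. At the injection visit, complete consent and baseline, then the 55 ml draw, then web randomisation, then true or sham processing and injection. State in the eligibility or randomisation section that a completed draw precedes allocation, and define what counts as a failed draw.
2. Log failed draws separately as eligible but not randomised, with the reason. Report uptake (willing among eligible) and draw failure (failed among bled) alongside the overall conversion rate.
3. Reconcile the follow-up origin between Trial design and setting and Data collection. Randomising on the day of injection makes the two agree. This step does not depend on moving the draw.

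**Cost.** Existing steps are re-ordered, with no new procedure or staff, and participant blinding is kept because everyone is bled anyway. The conversion rate falls slightly, and the comparison applies to people with a successful draw. The change does not remove failures of APS processing or dropout during the 15 to 20 minutes of preparation. Both would still follow randomisation and should be recorded by arm.
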